#### **A. Resistance/strengthening**

**All participants will be instructed to perform resistance/strengthening exercises for a 30-minute period at least twice a week.** The goal is to achieve moderate

exercise intensity (12-13 on the Borg Rating of Perceived Exertion (RPE) scale, included in patients' study booklets). The strengthening exercises used in this study are designed to engage proximal upper body muscles, shoulder muscles, abdominal muscles, back extensor muscles, and hip and leg muscles. Strengthening these muscle groups will develop the participant's trunk control and balance, which we believe will help with mobility during the prehabilitation phase and in the post-operative period. Furthermore, maintaining and developing the shoulder, back and leg muscles are important for transitional activities such as transferring into and out of bed, which is important after an extensive abdominal surgery such as a pancreatectomy.

**Participants will be instructed to perform any 8 strengthening exercises for a total duration of 30 minutes.** Each patient will be issued a set of 3 resistance exercise tubes with which the exercises can be performed. The strengthening exercises consist of seated and standing weight-bearing exercises. A variety of exercises targeting different muscle groups will be prescribed to minimize plateauing, and to generate increased interest and motivation (and thus, adherence). Participants will perform 3 sets of 8-12 repetitions each of each exercise. Once they are able to perform 3 sets of 12 repetitions of an exercise, they will graduate to the next level of increasing resistance as denoted by the color of the resistance tube used.

Prior to initiating the strengthening exercises, each participant will initiate a series of 5 *standing warm-up exercises* before each resistance exercise session that will help with balance.

Participants will select the 8 exercises to be performed from 19 strengthening exercises that include:

- *Upper body strengthening exercises* consist of seated and standing exercises to strengthen the deltoids, triceps, biceps, and rotator cuff. These exercises will include (but are not limited to) bench press, chest press, and biceps curls using resistance tubes.
- *Abdominal strengthening exercises* that will be performed while seated or standing using resistance tubes, which will be more tolerable as older adults may not be able to tolerate the supine-position abdominal exercises.

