### **B. Walking program**

**The walking program will consist of walking briskly for a duration of 20 - 30 minutes per day, with a frequency of at least 3 times per week.** The goal is to achieve a moderate intensity of exercise (Borg RPE of 12 - 13). If the participant is unable to tolerate walking briskly, they will be instructed to walk at a tolerable pace for 20 to 30 minutes during each walking session. Each participant will be provided a pedometer and will be instructed to record the number of steps taken each day in addition to the total time spent during each walking session.

The participants will be provided with exercise logs (both electronic, using MD Anderson's Research Electronic Data Capture - REDCap – system, and paper forms) in which they will record their daily physical activity. Participants will choose whether to record daily physical activity and exercise activities using REDCap or paper logs.

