### ***Adherence/compliance***

To monitor for adherence and screen for any exercise intolerance or exercise barriers, all participants will be contacted by the research staff via telephone every two weeks. The research staff will be provided with a list of screening questions (attached) to address exercise adherence and assess for the need to advance the strengthening program. The research staff will also implement behavior interventions to encourage continued adherence to the exercise program that will include education on the benefits of exercise and physical activity.

It is anticipated that a fully adherent participant would be able to complete at least 60 minutes of moderate-intensity walking and 60 minutes of moderate-intensity resistance exercise per week. Adherence to the program will be based on completion of a variety of strengthening exercises (eight or more per session) and the total time spent performing both the walking and strengthening components. A participant who is able to complete 60 minutes of walking and 60 minutes of resistance exercise per week during each phase of neoadjuvant therapy will be classified as 100% adherent during that phase.

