## **VII. Statistics**

This is a pilot study to assess the feasibility of a provider-supervised prehabilitation program among pancreatic patients who are undergoing neoadjuvant therapy. The prehabilitation program will include both exercise and nutrition interventions, where the exercise intervention will incorporate resistance/strengthening and walking programs. Adherence will be defined as the ability of each patient to complete  $\geq 60\%$  of the planned exercise intervention based on the total time spent performing the exercises relative to the total duration of therapy or total duration of recovery for a given phase. The primary endpoint, feasibility, will be established if  $\geq 60\%$  of the patients are adherent during a phase of therapy. That is, the prehabilitation program is deemed as feasible during a specific phase of therapy if 60% or more of the participants complete at least 60% of the weekly prescriptions for 60 minutes of walking and 60 minutes of strengthening

exercises during that phase of therapy. The calculation will account for the potential difference in the length of therapy among patients. The target weekly total exercise hour will be 120 minutes (including 60 minutes of walking and 60 minutes of strengthening exercises), thus we can derive the total prescribed hour for a given patient in a given phase considering his/her total treatment or recovery duration for that phase. Then, based on the recorded total hours of exercise intervention for that patient, we can calculate the % of completion for that patient in a given phase. If the % is at least 60% for a phase, we would define that patient as “adherent” for that phase. For the primary analysis, we will analyze the % adherence by phase, where “phase” could be chemotherapy phase, chemoradiation phase or recovery phase. As a secondary analysis, we will further differentiate whether patients receive chemoradiation from start or chemoradiation is given following chemotherapy and analyze these two subgroups of patients separately. Similarly, we will differentiate patients in recovery phase based on the therapies they receive prior to the recovery (i.e., chemotherapy only, chemoradiation only or chemotherapy plus chemoradiation).

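### The adherence calculation pools walking and strengthening minutes with no floor or cap per component, so 72 min/week of walking alone counts as adherent, and the protocol's other wordings of the endpoint can score the same patient differently.

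*Protocol*

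**What the plan says.** Section VII (Statistics) sets out the calculation. The denominator is a single weekly total: "The target weekly total exercise hour will be 120 minutes (including 60 minutes of walking and 60 minutes of strengthening exercises"), multiplied by the length of the phase. The numerator is also a single total: "based on the recorded total hours of exercise intervention for that patient, we can calculate the % of completion for that patient". The cut-off applies to that one percentage: "If the % is at least 60% for a phase, we would define that patient as" adherent. A phase is feasible if at least 60% of patients are adherent in it.

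The same section also puts the rule in words. A phase counts as feasible on this condition: "60% or more of the participants complete at least 60% of the weekly prescriptions for 60 minutes of walking and 60 minutes of strengthening" work.

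The Adherence/compliance part of Section VI opens differently: "Adherence to the program will be based on completion of a variety of strengthening exercises (eight or more per session"), together with the total time spent on both components. It describes full adherence as 60 minutes of walking and 60 minutes of resistance exercise per week.

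The prescriptions are also in Section VI. Walking is "walking briskly for a duration of 20 - 30 minutes per day, with a frequency of at least 3 times per week". For strengthening, participants are to "perform resistance/strengthening exercises for a 30-minute period at least twice a week".

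**The concern.** The intervention has two parts, resistance exercise and walking, and the protocol gives resistance work its own rationale: trunk control, balance, and transfers after abdominal surgery. A pooled percentage lets surplus minutes in one part make up for missing minutes in the other. Walking is the likelier source of surplus, because three sessions a week at the prescribed length already give 60 to 90 minutes while the denominator allows for 60.

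Feasibility is the sole primary endpoint, and the phase-specific rates are meant to guide later studies. If a phase can pass mainly on walking, its result says little about whether patients can do the resistance part in that phase. Section VII plans no separate adherence rate for each component, so the stated analyses would not show this.

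**Working it through.** **Inputs.** From Section VII: 60 + 60 = 120 min/week, a patient cut-off of 60%, a phase cut-off of 60% of patients, and phase sizes of 40, 45 and 50. From Section VI: walking 20-30 min at least 3 times a week; strengthening 30 min at least twice a week.

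**The plan's own figures.** Exact (Clopper-Pearson) 95% intervals for 24/40, 27/45 and 30/50 are 43.3%-75.1%, 44.3%-74.3% and 45.2%-73.6%. After rounding these match the stated intervals. The precision statement is correct and is not affected by this point.

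**The bar.** 0.60 x 120 = 72 min/week, averaged over the phase.

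**Scores by the Section VII calculation** (score = weekly minutes / 120):

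| Weekly pattern | Minutes | Score | Adherent, pooled | At least 36 min in each |
|---|---|---|---|---|
| Walk 3 x 20, no strengthening | 60 | 50% | no | no |
| Walk 3 x 24, no strengthening | 72 | 60% | yes | no |
| Walk 4 x 20, no strengthening | 80 | 66.7% | yes | no |
| Walk 3 x 30, no strengthening | 90 | 75% | yes | no |
| No walking, strengthen 3 x 30 | 90 | 75% | yes | no |
| Walk 36, strengthen 36 | 72 | 60% | yes | yes |

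The last column reads the in-words rule as 60% of each component: 0.60 x 60 = 36 min. Rows 2 to 5 are scored differently under the two readings. Rows 2 to 4 lie within the walking prescription. A phase would be declared feasible if 24 of 40, 27 of 45 or 30 of 50 patients behaved like any of rows 2 to 5.

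**Direction.** A patient with at least 36 min in each component has at least 36 + 36 = 72 in total. Pooled adherence can therefore never be below both-component adherence.

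**Size, for illustration only.** The protocol gives no component minutes, so these are assumptions: bivariate normal weekly minutes, with values below 0 set to 0.

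| Walking mean (SD) | Strengthening mean (SD) | Correlation | Pooled at least 72 | Both at least 36 | Pooled-adherent with zero strengthening |
|---|---|---|---|---|---|
| 90 (45) | 30 (30) | 0.3 | 80% | 39% | 7.6% |
| 75 (40) | 30 (30) | 0.3 | 74% | 38% | 5.5% |
| 60 (40) | 60 (40) | 0.5 | 76% | 59% | 0.5% |

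The chance of observing at least 60% adherent in 40 to 50 patients follows from the binomial distribution. In the first row it is above 99.9% pooled and under 1% on the both-component rule. In the third row it is about 99% pooled and about one half on the both-component rule.

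**The case against.** The best defence is that the text is more consistent than it first looks. The Adherence/compliance section refers to the total time over both components, so on time it agrees with the pooled calculation. The in-words rule, "complete at least 60% of the weekly prescriptions for 60 minutes of walking and 60 minutes of strengthening" exercises, can be read as 60% of the combined prescription, and the sentences around it speak of total time and a 120-minute target. A reader might infer that the protocol plainly defines adherence per component and then contradicts itself. The documents do not support that: the sentence is ambiguous, and the one firm discrepancy of wording is the eight-exercise condition. This stands. What remains is that the sentence permits two readings that score some patients differently, and that the calculation carries no safeguard for either component.

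A reader might also infer that anyone who skips strengthening is scored adherent. That is too strong: the patient must average at least 72 min/week of walking, and the minimum of 3 x 20 min scores 50% and fails.

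Nor does the illustration show that most adherent patients would do no strengthening. Under its assumptions only 0.5% to 7.6% of patients are adherent with none. Most of the gap comes from patients who do some strengthening but less than 36 min, and the low-strengthening scenarios place the assumed mean (30) below that cut-off.

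Finally, this is a pilot meant to find the best phase for the intervention, and the component minutes are logged separately, so either version could be computed afterwards. That makes the repair easy. It does not settle which version decides feasibility, and that choice should be made before the data are seen.

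**Conclusion.** The point holds in this form. The stated calculation sets a bar of 72 min/week of any mix, so a patient averaging that much walking with no strengthening is adherent, and the reverse is also true. The in-words rule and the eight-exercise condition can give a different answer for the same patient. The primary endpoint does not have one consistent definition, and the pooled version can call the two-part program feasible when strengthening is largely not done.

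The 72-minute result and the direction of the difference follow from the protocol's own figures and need no assumption. The size does: the range of 80% v 39% (low strengthening) to 76% v 59% (balanced components) rests on assumed minutes. It shows that the choice of definition could change the verdict for a phase. It does not show that it will.

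**What to change.** Reconcile the Adherence/compliance section and Section VII into one definition that does not let surplus minutes in one component replace the other.

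- **Preferred:** for each phase, compute walking minutes / (60 x weeks) and strengthening minutes / (60 x weeks), and call a patient adherent only if both are at least 60%. This is one reading of the protocol's own in-words rule.
- **More lenient alternative:** keep the pooled percentage but credit each component with at most 60 min/week. One component alone then scores at most 60/120 = 50%, but with walking at 60 min only 72 - 60 = 12 min/week of strengthening is needed. In the first two scenarios above this gives 66% and 62% adherent. If it is chosen, state whether the cap applies week by week or to the phase total.

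Under either definition, report the walking and strengthening adherence rates separately for each phase with exact 95% intervals, keep the pooled percentage as a secondary figure, and report the eight-exercise condition descriptively.

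No new data are needed, because Section VI already has participants record strengthening time and walking time separately. The cost is that the reported adherence rate will be equal or lower against the same 60% feasibility bar. The preferred rule also fails some patients who meet the total target: 90 min of walking with 30 min of strengthening is 120/120 = 100% pooled, but 30/60 = 50% for strengthening. The protocol should acknowledge this when the definition is fixed.

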#### ***Initial Assessment of Exercise Tolerance***

All enrolled patients will complete the remainder of the PROMIS Physical Function 12a Short Form and participate in two physical screening tests to determine participation in the exercise and nutrition interventions and to evaluate exercise tolerance.

- PROMIS questions PF6, PFC29, PFA55, PFC53, PFA9 and PF\_23 must be answered with a 5, 4 or 3 to participate in the exercise and nutrition interventions.
- Any answer of 1 or 2 on the PROMIS will result in the patient being excluded from participation.
- Patients must be able to perform the following tests to participate in the exercise and nutrition intervention. Patients who cannot perform both tests will be excluded from participation.
  - 5x sit-to-stand
  - 6 minute walk test (6MWT)

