The study was originally designed to enroll 50 patients and as of August 2015, 20 patients have been enrolled under this initial design. We have placed the study on hold until these attached revisions are made because we have encountered several issues with the first design and have identified solutions to these problems. The primary issue is that, under the old design, we would assess the exercise intervention in a 6-week period regardless of the treatment phase. Initial analysis of the data has shown us that patients’ adherence depends to a large degree on the phase of therapy. For example, patients seem to be less compliant with exercise during chemotherapy than they are during either chemoradiation or rest. Future trials will require us to time the intervention precisely and optimize the intervention during preoperative therapy, so we need to know the best “phase” (or phases) of therapy to deliver the exercise intervention. This trial will allow us to gain a more accurate and better understanding about patients’ adherence during each phase so as to guide the focus for future studies.

We have also changed a couple of the survey tools and assessments we will use in this new design, as described below. We added tools to help us explore barriers to exercise and we improved a physical assessment from one with low resolution to one with higher resolution (and, it is used more frequently in the literature).

Under the revised design, we will enroll 50 new patients and evaluate the feasibility of the exercise intervention through assessing their adherence rate during each phase of the neoadjuvant therapy. We assume that among the 50 patients, 35 patients will receive chemo followed by chemoradiation, recovery and then surgery; 10 patients will receive chemoradiation followed by recovery phase and then surgery; and 5 patients will receive chemotherapy followed by recovery phase and then surgery. Therefore, overall we will have 40 patients’ data for assessing the adherent rate in the chemotherapy phase, 45 patients’ data for assessing the adherent rate in the chemotheradiation phase and 50 patients’ data for the recovery phase. Thus, with a sample size of 40, 45 and 50 and assuming an adherence rate of 60%, the exact 95% confidence interval will be (43%, 75%), (44%, 74%) and (45%, 74%), respectively.

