We aim to recruit roughly equal numbers of male and female participants and participants who met/exceeded or did not meet baseline recommendations for walking and resistance exercise. However, we recognize that differences in interest and availability can affect recruitment, and we may have imbalances in these proportions. Recent qualitative research studies examining influences and outcomes related to physical activity among cancer survivors have reached saturation of themes after interviewing five [12] and nine [13] participants. Ten of the 20 patients enrolled in the original 2014-0702 prehabilitation protocol underwent surgery, and we expect approximately 50% of the 50 patients who have enrolled or will enroll in the current (revised) protocol to undergo surgery. Therefore, we will have access to approximately 35 patients who are possible candidates for this study. We expect to conduct approximately 12-15 interviews among this group. Qualitative analysis of interview transcripts will occur on a rolling bases, however, and we will end recruitment and cease interviewing upon reaching saturation of qualitative themes.

The following is a list of interview topics and questions:

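### The per-phase sizes of 40, 45 and 50 are maxima stated as expected values: they allow for neither the protocol's own 50% surgery expectation nor its exclusions after enrolment

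*Protocol*

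**What the plan says.** All references are to the prehabilitation protocol 2014-0702, the second part of the Protocol document.

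VII. Statistics sets the size: "Under the revised design, we will enroll 50 new patients". It assumes three treatment sequences that together account for all 50 patients. The largest is given as "35 patients will receive chemo followed by chemoradiation, recovery and then surgery". Two smaller groups, 10 treated with chemoradiation only and 5 with chemotherapy only, are likewise taken through recovery to surgery. The stated precision is 43% to 75% for chemotherapy, 44% to 74% for chemoradiation and 45% to 74% for recovery, on this basis: "with a sample size of 40, 45 and 50 and assuming an adherence rate of 60%, the exact 95% confidence interval will be".

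The text on qualitative interviews under Study Measures gives a different expectation for the same cohort: "we expect approximately 50% of the 50 patients who have enrolled or will enroll in the current (revised) protocol to undergo surgery". It rests on experience with the first design: "Ten of the 20 patients enrolled in the original 2014-0702 prehabilitation protocol underwent surgery".

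Initial Assessment of Exercise Tolerance applies to patients who are already enrolled. A PROMIS answer of 1 or 2 bars them from the exercise and nutrition programme, and for the sit-to-stand and six-minute walk tests it says: "Patients who cannot perform both tests will be excluded from participation". No replacement of these patients and no allowance for them is stated.

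**The concern.** The primary endpoint is the proportion of adherent patients in each phase, and the sample size is justified only by the width of three confidence intervals. If the sizes behind those intervals cannot be expected, the justification promises more than the design delivers.

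Two losses are written into the protocol but left out of the calculation. First, every assumed sequence ends in surgery, while another section expects about half of these patients to have it. Second, enrolling 50 patients does not give 50 exercisers, because a further assessment follows enrolment. At stake is the precision of the per-phase adherence rates, and so of the comparison of phases that is meant to guide later trials.

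**Working it through.** **1. The plan's own figures.** From the assumed sequences (35, 10 and 5):

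- chemotherapy: 35 + 5 = 40
- chemoradiation: 35 + 10 = 45
- recovery: 35 + 10 + 5 = 50

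The exact (Clopper-Pearson) 95% interval for x adherent of n has as its lower limit the 2.5% quantile of Beta(x, n − x + 1) and as its upper limit the 97.5% quantile of Beta(x + 1, n − x). With x = 0.60 × n:

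| Phase | x/n | Exact 95% CI | Stated |
|---|---|---|---|
| Chemotherapy | 24/40 | 43.3% to 75.1% | 43%, 75% |
| Chemoradiation | 27/45 | 44.3% to 74.3% | 44%, 74% |
| Recovery | 30/50 | 45.2% to 73.6% | 45%, 74% |

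All three reproduce. The question is the input n.

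**2. Recovery and the surgery rate.** The expected number with surgery is 0.50 × 50 = 25. The interview text uses this figure itself: its pool of about 35 candidates is 10 from the first design plus 25 from the new 50. If only those patients supplied recovery data, n would be 25. If all supplied it, n would be 50. A 75% case is added as an assumption (37.5, taken as 38).

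| Share reaching recovery | x/n | Exact 95% CI | Width (points) |
|---|---|---|---|
| 100% | 30/50 | 45.2% to 73.6% | 28.4 |
| 75% (assumed) | 23/38 | 43.4% to 76.0% | 32.6 |
| 50% | 15/25 | 38.7% to 78.9% | 40.2 |

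The ratio of the extreme widths is 40.2 / 28.4 = 1.4.

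**3. Exclusion after enrolment, all phases.** The protocol gives no failure rate, so 10% and 20% are assumptions. Both n and x are rounded to whole patients. The observed rate is therefore not exactly 60% in every row, and the limits do not move perfectly evenly.

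| Phase | 10% excluded | 20% excluded |
|---|---|---|
| Chemotherapy | 22/36: 43% to 77% | 19/32: 41% to 76% |
| Chemoradiation | 24/40: 43% to 75% | 22/36: 43% to 77% |
| Recovery, all reach it | 27/45: 44% to 74% | 24/40: 43% to 75% |
| Recovery, half reach it | 13/22: 36% to 79% | 12/20: 36% to 81% |

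**4. Effect on the decision rule.** Feasibility is declared when at least 60% of patients in a phase are adherent. If true adherence were 50% (an assumption), the binomial chance of reaching that cut-off is 0.10 with n = 50 (30 or more) and 0.21 with n = 25 (15 or more). A smaller n makes the rule noisier, although no interval enters it.

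**The case against.** The strongest reply is that nothing has been miscalculated. VII. Statistics labels the split as an assumption, the intervals follow from it, and the final report will give exact intervals from the patients actually observed. Optimistic planning therefore does not carry into the results. This is a pilot without a hypothesis test, and feasibility is judged on a point estimate. All of that stands, and it limits the weight of the point. It does not remove the conflict between two expectations for the same 50 patients.

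Three stronger readings are tempting, and the documents do not support them.

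- **That the surgery rate undermines all three sizes.** Surgery follows every phase, so a 50% rate does not by itself reduce the chemotherapy or chemoradiation counts.
- **That recovery will have 25 patients.** The interview text provides for patients who completed the exercise programme and were not resected, approached after preoperative restaging. The number reaching recovery can therefore exceed the number having surgery, and 25 is only a pessimistic bound.
- **That dropouts leave the denominator and inflate adherence.** VII. Statistics divides each patient's recorded hours by the hours prescribed for that patient's full time in the phase. A patient who stops exercising or logging while the phase continues still accrues prescribed hours and falls towards non-adherence. Only withdrawal from the exercise programme is left unstated, and such detail may properly sit in an analysis plan.

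The loss after enrolment may also be smaller than it looks. Exclusion criterion 2 (section V) already bars patients who cannot complete the baseline questionnaires or functional assessments, and Final Enrollment requires all criteria to be met first. The overlap is mainly with the functional tests. Only the first PROMIS question is used before enrolment, so exclusion on the remaining items still falls on enrolled patients.

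**Conclusion.** The concern holds as a mismatch between the stated sizes and the protocol's own expectations. The sizes 40, 45 and 50 are the most the design can yield from 50 enrollees under the assumed 35/10/5 split, and they are presented as what it will yield.

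The effect is largest in recovery. Before exclusions after enrolment, the interval at 60% adherence lies between 45-74% and 39-79%, up to 1.4 times as wide as stated. For chemotherapy and chemoradiation the effect comes only from those exclusions and is modest at an assumed 10-20%. The recovery range rests on the protocol's approximate 50% surgery rate and on the unknown share of unresected patients who complete recovery.

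The consequence is lower precision than advertised. It is not a bias in the endpoint or a loss of error control, and it should be ranked as a clarification worth making rather than a flaw that stops the trial.

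**What to change.** 1. Reconcile the three places: the pathway split in VII. Statistics, the surgery expectation in the interview text under Study Measures, and the assessment of already-enrolled patients under Initial Assessment of Exercise Tolerance. State whether the 50 are counted before or after that assessment, and whether patients removed by it are replaced.
2. Label 40, 45 and 50 as maxima. Give the expected n and exact interval for each phase as a range with the attrition assumption beside it. For recovery before exclusions, for example: n of 25 to 50, interval 39-79% to 45-74%.
3. Optionally, add one sentence that the hours-over-duration rule also applies to patients who entered a phase and then withdrew from the exercise programme.

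The cost is a few sentences in the statistics section and wider stated intervals. Restating the precision needs no extra patients.

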Descriptive statistics, such as frequency (percentage) and median (range) will be used to summarize the data, including patient demographics, clinical features, comorbidity,

symptoms burden and quality of life. We will also summarize patients' tolerance for specific exercises, their ability to advance the exercises and the motivating/prohibiting factors for them to complete the study materials. The rate of adherence will be estimated for each phase, along with the exact 95% confidence interval. Similarly, the proportion of patients with frailty (i.e., abnormality in 3 or more of 5 markers), perioperative complications (yes/no; high/low grade) and physical/functional measures (yes/no for completing the 5x sit-to-stand test and the 6-minute walk test) will be estimated, along with the exact 95% confidence intervals. As an exploratory analysis, we will fit a multiple logistic regression model to assess the association between patient characteristics and socioecological characteristics (social support for exercise and neighborhood walkability) and adherence (yes/no) for each phase. In addition, paired t-test or Wilcoxon signed rank test will be used to assess the change of Fact-Hep, Frailty, physical functioning, and exercise capacity measures from baseline. We will also fit a linear mixed model to assess the change of each measurement over time (i.e., at enrollment, pre-op and post-op visit), while accounting for the correlation among multiple observations from the same patient.

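### The exploratory model for predictors of adherence uses a yes/no cut at 60%, although percent completion is already derived; modelling the percentage would use 40 to 50 patients per phase better

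*Protocol*

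**What the plan says.** All of this is in section VII, Statistics, of the prehabilitation protocol (2014-0702).

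- Recorded exercise time is set against 120 prescribed minutes a week over the length of the phase, so that "we can calculate the % of completion for that patient in a given phase".
- That percentage is then cut: "If the % is at least 60% for a phase, we would define that patient as “adherent” for that phase". The program is feasible in a phase if at least 60% of patients are adherent.
- The predictor analysis is labelled exploratory: "we will fit a multiple logistic regression model to assess the association between patient characteristics and socioecological characteristics". Its outcome is fixed as "and adherence (yes/no) for each phase". The predictors are patient characteristics, social support for exercise and neighborhood walkability.
- The revised design expects 40, 45 and 50 patients in the chemotherapy, chemoradiation and recovery phases, and plans on 60% adherence.
- On the revised instruments it says: "We added tools to help us explore barriers to exercise".

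No model of percent completion is planned. No effect size, significance level, number of predictors or power is given for the logistic model.

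**The concern.** The 60% cut answers one question: do enough patients reach the threshold in this phase? The predictor analysis asks another: which characteristics go with doing more or less of the program? For that second question a patient at 5% and one at 59% are coded alike, and so are patients at 61% and 100%.

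With 40 to 50 patients per phase there is little information to spare. The logistic model is the only model the protocol names that uses the social-support and walkability scales. At 60% adherence there are 16, 18 and 20 non-adherent patients per phase. Under Study Measures, the social-support scale and four walkability subscales would already make five terms if entered separately. That leaves 16/5 = 3.2, 18/5 = 3.6 and 20/5 = 4.0 non-adherent patients per term, before any patient characteristic is added. What is at stake is a moderate association that the same data could show but the yes/no model misses.

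**Working it through.** **1. The plan's own figures.** Exact (Clopper-Pearson) 95% intervals for 24/40, 27/45 and 30/50 are (43.3%, 75.1%), (44.3%, 74.3%) and (45.2%, 73.6%). These match the stated (43%, 75%), (44%, 74%) and (45%, 74%). The plan gives no power figure for the predictor model.

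**2. Inputs.** From section VII: n = 40, 45, 50 and adherence p = 0.60. Assumed, because the protocol gives none: two-sided alpha 0.05, normal latent completion, correlation r of 0.2 to 0.5 between predictor and completion, and one or five predictors.

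**3. Information kept by the cut.** Efficiency = φ(c)² / [p(1−p)], where c is the normal cut-point for p. At p = 0.60, c = 0.253 and φ(c) = 0.386, so efficiency = 0.149 / 0.24 = 0.62. Effective sample sizes are 40 × 0.622 = 24.9, 45 × 0.622 = 28.0 and 50 × 0.622 = 31.1. The result depends on the adherence rate: the formula gives 64% at p = 0.50, 58% at 0.70 and 49% at 0.80.

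**4. Power, one predictor.** Power ≈ Φ(√(m−3) · atanh(r) − 1.96), with m = n for percent completion and m = 0.622n for yes/no. Example with n = 40, r = 0.4: √37 × 0.4236 − 1.96 = 0.617, giving 73%; √21.9 × 0.4236 − 1.96 = 0.02, giving 51%.

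| r | Percent completion, n = 40/45/50 | Yes/no | Loss, points |
|---|---|---|---|
| 0.2 | 23 / 26 / 28% | 16 / 17 / 19% | 8 to 10 |
| 0.3 | 47 / 52 / 56% | 30 / 34 / 38% | 16 to 19 |
| 0.4 | 73 / 78 / 83% | 51 / 56 / 61% | 21 to 22 |
| 0.5 | 92 / 95 / 97% | 73 / 78 / 83% | 13 to 19 |

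**5. Simulation, five predictors, r = 0.4, normal completion (1,500 runs per cell).**

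| n | Linear on percent | Logistic, Wald | Logistic, likelihood ratio |
|---|---|---|---|
| 40 | 70% | 47% | 55% |
| 45 | 75% | 51% | 58% |
| 50 | 80% | 59% | 65% |

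Across n, the Wald loss is 14 to 18 points at r = 0.3, 21 to 23 at 0.4 and 15 to 19 at 0.5. The likelihood-ratio loss is about 7 to 12, 15 to 17 and 11 to 12 points. At r = 0.2 the losses are 6 to 8 (Wald) and 2 to 4 (likelihood ratio). The likelihood-ratio test had a type I error of about 7 to 8%, so its power is somewhat flattered.

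**6. Departures from normality.** Clipping completion to 0–100% generally lowers the loss by only a few points. With n = 50 and r = 0.4, linear regression has 77%, against 58% (Wald) and 64% (likelihood ratio). Under an assumed strong right skew with n = 40 and r = 0.4, linear regression with robust standard errors had 47% power against 54% for logistic, so the gain was gone; rank-based regression kept 66%.

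Taken together, r = 0.3 to 0.5 gives roughly 6 to 24 points. The ends are approximate. One simulated cell (one predictor, n = 40, r = 0.4, clipped, Wald) reached 73.5 − 47.2 = 26.3, and the Monte Carlo standard error of a single percentage is up to √(0.25/1500) = 1.3 points.

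**The case against.** The plan contains no misstatement here. The model is labelled exploratory, its outcome is the protocol's own definition of adherence, and asking who reaches the feasibility threshold is a coherent question in a pilot. That stands, and it is why the logistic model should be kept.

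The size of the loss also rests on chosen effect sizes and a chosen distribution. Under strong right skew, a linear model with robust standard errors can do no better than logistic regression, or worse. That stands too, and it decides which form of continuous model to recommend.

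A further argument is that percent completion is a different outcome. Pooled minutes can be raised by walking alone, the Adherence/compliance section also mentions eight or more exercises per session, and no cap at 100% is stated. This carries less weight. Section VII cuts the same pooled percentage to define adherence, so the yes/no outcome inherits the first two limits. The missing cap does matter for an untransformed linear model, and less for a rank-based one.

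Finally, the protocol also examines barriers through qualitative interviews, so this model is not the only source on them.

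A reader might infer that the plan contradicts itself, that a loss of 10 to 20 points is established, or that the feasibility finding is weakened. The documents support none of these. They give no effect size or distribution for this analysis, and the feasibility rule rests on the 60% threshold and exact intervals, which the predictor model does not enter.

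**Conclusion.** The point holds as a minor improvement to an exploratory analysis. The plan fixes a yes/no outcome where it already has the percentage. With normal latent completion and 60% adherent, the cut discards about 38% of the information. For predictors correlated 0.3 to 0.5 with completion, the cost is roughly 6 to 24 points of power, varying with the test and the shape of the distribution. Weak predictors (r about 0.2) lose less and stay below 30% power on either scale. The advantage is not guaranteed: under strong skew it depends on using a rank-based or transformed analysis. The primary endpoint and its conclusion are unaffected.

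**What to change.** Leave the yes/no endpoint, the 60% feasibility rule and the exact intervals as they are. In the sentence on the exploratory predictor analysis, make the main model a regression of percent completion in each phase on the same predictors. State that rank-based or suitably transformed linear regression will be used if completion is skewed; robust standard errors alone are not enough, because they can remove the gain. Report the logistic model alongside it as the analysis tied to the feasibility threshold.

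The cost is about one sentence in section VII and no new data, since the percentage is already derived. The downside is interpretation: the main coefficients would be on a completion or rank scale instead of odds ratios.
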